### Statistical analyses

The baseline characteristics of completers and drop outs during follow-up will be compared by means of an independent t-test for continuous data and by Chi Square analysis for categorical data. Any significant differences (*p* < 0.05) in baseline characteristics between intervention and control group will be controlled for in the subsequent analyses. All analyses will be based on the intention-to-treat principle.

For the main analyses, multilevel regression models for repeated measures (mixed models) will be used to evaluate changes in primary outcome variables across time between intervention and control group and to evaluate changes in secondary outcomes across time in the intervention group. Temporal associations between change in secondary outcomes that may be potential mechanisms and change in primary outcomes will be examined by linear regression analyses, in which decrease in primary outcome scores are predicted by earlier changes in secondary outcome scores (and vice versa to control for potential reversed effects). Tertiary outcomes will be compared between intervention and control group using independent t-tests for continuous data and Chi Square analyses for categorical data.

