## Method/design

### Design and setting

The current study is a parallel group, two-arm, superiority randomized controlled trial (RCT) with equal allocation of participants and a repeated measures design. Table 1 shows the overall study design. The trial is part of a large longitudinal cohort study among pregnant women (The Brabant Study). Within the Brabant Study up to 4000 pregnant women are followed from 12 weeks of gestation until 8 to 10 weeks postpartum. The current trial targets a specific sub-group of pregnant women with symptoms of psychological distress, specifically depression and anxiety and is conducted in the South-East part of North-Brabant in the Netherlands. The trial is registered at clinicaltrials.gov (2018-CDE-9318) and was approved of by the Ethics Committee of the University of Amsterdam. Any trial amendments will be approved of by the Ethics Committee of the University of Amsterdam before implementation and will be reported to the trial registry.

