#### Additional outcome measures

##### Demographic data

As part of the Brabant Study, demographic data such as age, marital status, ethnicity, education, working status and number of the children in the home will be collected via online questionnaires.

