### Procedure

Within the Brabant Study, women will receive their first questionnaire (related to obstetrics and mental health) at 12 weeks of pregnancy via internet. Women with a score above the cut off on the EDS (> 7) and/or the NA scale of the TPDS (> 9) will be randomly allocated to the intervention or control group of the current study. Moreover, women with depressive symptoms that are too severe will not be included in the trial. These women are defined by an EDS score > 18. Also, women who did not answer the last question of the EDS (“The thought of harming myself has occurred to me”) with “never” will not be included in the trial. Instead, author LH will send an e-mail to encourage these women to seek help with their general practitioner (GP).

LH monitors the scores on the EDS and TPDS and, when a woman scores above cut off, passes on the corresponding participant number to author MM who has no further involvement in the practical recruitment, enrolment and assessment of patients in the trial. MM will refer to a list of random numbers of 1 (intervention) and 2 (care as usual), which will be created by MM using the Statistical Package of Social Science (SPSS), version 24. The random numbers will be sequentially assigned to subsequent participants. MM will inform LH about the allocation by e-mail and will archive the allocations in a secured document on her computer. LH will document the allocation in the general inclusion database, which will be checked by MM. LH will contact and invite the women in the intervention group by e-mail to participate in the online MBI course. The control group will receive care as usual and will fill out the questionnaires according to the Brabant Study. Women in both the intervention and control group have already provided written informed consent for participation in the Brabant Study. The above described procedure of randomization will ensure objectivity of the researcher and will eliminate bias in the participants’ group allocation. Blinding of participants or researchers is not possible due to the study design.

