The women allocated to the intervention group will receive an information letter about the trial and the online MBI course by e-mail. Women will be asked to respond by e-mail whether they want to participate. When women agree to participate, they will sign a full written informed consent, which will be sent by post. After signing the informed consent, women will fill out questionnaires via internet, which will be around 16 weeks of pregnancy. Besides the standardized questionnaires, women will be asked whether they have had any previous experiences with mindfulness. Subsequently, women will start the 8-week online MBI course, followed between 16 and 28 weeks of pregnancy. Women in both the intervention and control group are not prohibited to partake in any other pregnancy course. At 28 weeks of pregnancy (post intervention) women in both groups will be asked whether they took part, or are still taking part, in adjunctive pregnancy courses, to be able to control for this variable in statistical analyses.

Participating women fill out online questionnaires at different time points during pregnancy as shown in Table 2. Women in the intervention and control group fill out the questionnaires of the Brabant Study at baseline (12 weeks of pregnancy), halfway through the intervention (20 weeks of pregnancy) and post intervention (28 weeks of pregnancy). Moreover, women in the intervention group fill out extra questionnaires before intervention (16 weeks of pregnancy), halfway through the intervention, post intervention and after a follow-up period of 8 weeks (36 weeks of pregnancy).

**Table 2 Tab2:** Measurements and time points

	Concept	Questionnaire	Measurement time points											
			12 weeks		16 weeks		20 weeks		28 weeks		36 weeks		Childbirth	
			I	C	I	C	I	C	I	C	I	C	I	C
Primary	Pregnancy distress	EDS	X	X			X	X	X	X	X			
	Pregnancy distress	TPDS (NA)	X	X			X	X	X	X	X			
Secondary	Mindfulness skills	TFMQ-SF			X				X		X			
	Rumination	RRQ			X				X		X			
	Self-compassion	SCS-SF			X				X		X			
Tertiary	Obstetric data	Non-standardized											X	X
	Demographic data	Non-standardized	X	X										
	Evaluation intervention	Non-standardized							X		X			

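### Adjustment covariates are picked by between-arm baseline tests at p < 0.05, so the between-group model is not fixed in advance and prognostic variables are usually left out

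*Protocol article*

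**What the plan says.** The rule stands in the Statistical analyses section of the protocol article, just before the main models: any differences significant at p < 0.05 "in baseline characteristics between intervention and control group will be controlled for in the subsequent analyses". The next paragraph says that "multilevel regression models for repeated measures (mixed models) will be used to evaluate changes in primary outcome variables across time", comparing the two arms, so the rule governs the primary analysis. It also nominally covers the tertiary comparisons, although these are t-tests and chi-square tests, which cannot take a covariate.

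The article does not say which baseline characteristics will be tested. The Demographic data section gives an open list: "demographic data such as age, marital status, ethnicity, education, working status and number of the children in the home". Allocation is 1:1 from a random-number list with no stratification factor named (Design and setting: "randomized controlled trial (RCT) with equal allocation of participants and a repeated measures design"; Procedure: "The random numbers will be sequentially assigned to subsequent participants").

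Both arms "fill out the questionnaires of the Brabant Study at baseline (12 weeks of pregnancy), halfway through the intervention (20 weeks of pregnancy") and again at 28 weeks. The 12-week EDS and TPDS-NA are therefore the first of three repeated measures. The only other adjustment variable mentioned is participation "in adjunctive pregnancy courses, to be able to control for this variable in statistical analyses". That is asked at 28 weeks, after randomisation.

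**The concern.** A covariate is worth including because it predicts the outcome. A between-arm baseline test does not measure that. Under sound randomisation every null hypothesis tested is true, and a significant result is a 5% chance event. The rule thus brings in variables that happen to differ, even if irrelevant, and leaves out strong predictors that happen to balance.

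Two things are at stake. First, the covariate set of the between-group model is unknown until the data are seen. The list of candidates is itself open, and the trial is not blinded. Second, precision available from variables already collected is mostly not used.

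**Working it through.** **1. The plan's own figure.** The Sample size calculation section gives 206 women for a time by group interaction in a MANOVA with three time points, d = 0.5 and power 0.90. Alpha is not stated; 0.05 is assumed. With f = d/2 = 0.25, λ = N f² = 206 × 0.0625 = 12.875, df1 = 2 and df2 = 203, power is 0.901. The 206 reproduces, and the covariate rule plays no part in it.

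**2. How often the rule acts by chance.** With k independent tests at 0.05, the chance of at least one flag is 1 − 0.95^k.

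| Variables tested | k | Chance of at least one flag |
|---|---|---|
| Six named demographics | 6 | 26.5% |
| Those plus 12-week EDS and TPDS-NA | 8 | 33.7% |
| A longer list | 10 | 40.1% |

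Any single variable is flagged with probability 0.05 (0.048 to 0.051 in simulation), so a truly prognostic one is omitted about 95% of the time.

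**3. What the rule does to the test.** A simulation used 8,000 runs per setting, 103 women per arm, one endpoint and one covariate. The documents give no covariate–outcome correlation, so a range is assumed. The effect of d = 0.4 used for power is illustrative.

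| Correlation | Quantity | Unadjusted | Adjust only if p < 0.05 | Always adjust |
|---|---|---|---|---|
| 0.3 | Type I error | 0.052 | 0.049 | 0.048 |
| 0.5 | Type I error | 0.049 | 0.044 | 0.049 |
| 0.7 | Type I error | 0.047 | 0.034 | 0.049 |
| 0.3 | Power, d = 0.4 | 0.820 | 0.827 | 0.855 |
| 0.5 | Power, d = 0.4 | 0.816 | 0.828 | 0.910 |

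At correlation 0.5 the SD of the estimate is 0.140 unadjusted, 0.135 under the rule and 0.121 with adjustment fixed in advance. The rule recovers little of the available precision, and its error rate is at or below the nominal level.

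**4. A realistic size for this trial.** The 12-week score is already in the model, so only the extra variance explained by other covariates counts. The standard error is multiplied by √(1 − R²).

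- Additional R² = 0.05: √0.95 = 0.975, a 2.5% smaller standard error. The precision of 206 unadjusted women would need 206 × 0.95 ≈ 196.
- Additional R² = 0.10: √0.90 = 0.949, about 5% smaller. The equivalent is 206 × 0.90 ≈ 185.

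In the planned 2-df test, λ becomes 12.875/0.95 = 13.55 or 12.875/0.90 = 14.31, and power moves from 0.901 to 0.916 or 0.930. Here R² means variance of the tested contrast. A covariate entered only as a main effect largely cancels from a within-woman time contrast, so these gains require that it predicts change.

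**The case against.** The strongest defence is that the rule is itself written down in advance, has a fixed threshold, and selects on baseline data, never on the outcome. That is fair. A reader might infer that a model chosen on the data inflates the type I error. The simulation does not support this: the error is 0.034 to 0.049.

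A reader might also infer that baseline distress, probably the strongest predictor, is thrown away. It is not. The 12-week EDS and TPDS-NA are time points of the planned repeated-measures model, whatever their baseline p-values.

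A third tempting reading is a large loss of power. At 206 women and an assumed correlation of 0.5 between time points, a 1-df baseline-adjusted contrast at 28 weeks has power 0.985, a 1-df change contrast 0.946 and the planned 2-df interaction 0.901. The step from 0.901 to 0.946 is degrees of freedom, with λ = 12.875 in both. The step from 0.946 to 0.985 is change score against adjustment for the outcome's own baseline (λ = 12.875/0.75 = 17.17). Neither step measures the covariate rule, and both would remain if it were deleted.

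The percentages in step 2 assume independent tests, and the demographics are plausibly correlated. The list is open, so k is not known. Chance is also the only source of imbalance only if women are analysed as randomised. Consent to the course follows allocation, and the article expects 35% of the women allocated to it to agree. If consenters were compared with controls, differences would not be pure chance. That is a separate question of who is analysed, and a p < 0.05 screen would not repair it.

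Finally, a full covariate list may belong in an analysis plan not shown, so its absence is not the point. The stated selection rule is.

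**Conclusion.** The point stands in limited form. The article commits to choosing covariates by baseline significance, which is a poor rule, and that is not a detail left to another document. With women analysed as randomised and independent tests, the model changes by chance in about 26% of trials (six variables) to 34% (eight), while any given prognostic covariate is omitted in about 95%.

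The consequences are a between-group model that is not fixed until the data are seen, a slightly conservative test, and a modest loss of precision. The loss is about 2.5 to 5% of the standard error at an additional R² of 0.05 to 0.10, which is assumed because the documents give no figure. There is no case for an inflated type I error, for discarded baseline distress scores, or for changing the sample size of 206. The change is worth making because it is cheap, not because the trial's validity hangs on it.

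**What to change.** - Delete the p < 0.05 rule and the baseline tests between arms. Keep a descriptive baseline table.
- Before any outcome data are analysed, name a short set of covariates expected to be prognostic, measured before randomisation and already collected. Use it in every between-group model whatever the observed imbalance. Tying this to unblinding would not work, because the trial is not blinded. The article does not show which demographics predict distress, so the investigators should justify the set.
- State that the 12-week outcome enters once: either as a repeated measure with baseline means constrained equal across arms, or as a covariate with only the 20- and 28-week scores as responses. Adding it as a covariate while it stays among the responses would use it twice.
- If the 12-week score stays as a repeated measure, let the other covariates have effects that differ by time, so that they bear on the tested contrast.

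The cost is a few degrees of freedom and a small rewording of the model. No new data are needed and the sample size stays at 206. The article reports 28 women enrolled on 20 February 2020, with analysis only after trial completion.

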**Methods:**

The current study is a randomized controlled trial with repeated measures. Consenting women with elevated levels of pregnancy distress will be randomized into an intervention group (MBI) or control group (care as usual) around 12 weeks of pregnancy, with an intended sample size of 103 women in each group. The primary outcome, pregnancy distress, will be assessed via questionnaires at baseline, halfway through the intervention and post intervention in both intervention and control group, and after 8 weeks follow-up in the intervention group. Secondary outcomes are mindfulness skills, rumination and self-compassion, which are also seen as potential working mechanisms, and will be assessed via questionnaires before intervention, halfway through the intervention, post intervention and after 8 weeks follow-up in the intervention group. Tertiary outcome variables are obstetric data and will be collected from the obstetric records for both intervention and control group. Analyses will be based on the intention-to-treat principle. Multilevel regression models for repeated measures (mixed models) will be used to evaluate changes in primary and secondary outcome variables. Tertiary outcomes will be compared between groups using independent t-tests and Chi Square analyses.

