#### Tertiary outcome measures

##### Obstetric data

As part of the Brabant Study, data on pregnancy and delivery will be collected from the community midwife and/or obstetrician, by extracting these data from the obstetric form. This concerns obstetric data such as gestational age at birth, use of anesthesia, mode of delivery and birth weight.

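### The baseline-adjustment rule cannot be applied to the obstetric outcomes with the t-tests and Chi Square tests named for them; a regression with one covariate fixed in advance would settle it

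*Protocol article*

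**What the plan says.** Three statements in the protocol article bear on this.

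- **The adjustment rule** (Statistical analyses, first paragraph). Differences reaching p < 0.05 "in baseline characteristics between intervention and control group will be controlled for in the subsequent analyses". No outcome tier is excluded.
- **The tests for the obstetric outcomes** (same section, second paragraph). "Tertiary outcomes will be compared between intervention and control group using independent t-tests for continuous data and Chi Square analyses for categorical data". The abstract repeats this without qualification: "Tertiary outcomes will be compared between groups using independent t-tests and Chi Square analyses". The outcomes are given under Obstetric data: "This concerns obstetric data such as gestational age at birth, use of anesthesia, mode of delivery and birth weight".
- **The models for the other outcomes** (same section). "For the main analyses, multilevel regression models for repeated measures (mixed models) will be used" for the primary and secondary outcomes. These models can take covariates.

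The baseline characteristics are listed under Demographic data: "demographic data such as age, marital status, ethnicity, education, working status and number of the children in the home". Table 2 places their collection at 12 weeks in both arms, before allocation. The two distress scales, EDS and TPDS negative affect, are also measured at 12 weeks in both arms.

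**The concern.** The rule and the tests stand in one section, and once the rule is triggered they cannot both be followed. A t-test or a Chi Square test compares two groups and has no place for a third variable. The analyst would then have two options: leave the obstetric results unadjusted, against the rule, or replace the named test with a model that the protocol does not name, after seeing which characteristics are unbalanced. Under Data management, the person who will analyse the data is also the one who, under Procedure, records the allocations. Blinding is stated there to be impossible, so that choice would not be blind.

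A second, smaller cost is precision. Whether a woman already has children can be expected to predict birth outcomes (an assumption; the documents give no figures). The trial collects a close proxy for it, and the named tests leave it unused.

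**Working it through.** **1. The plan's own figure.** The only sample size stated is 206 (103 per arm), for the primary outcome. For a repeated-measures MANOVA interaction with 2 groups, 3 time points, f = d/2 = 0.25, λ = f²N, df1 = 2, df2 = N − 3 and two-sided alpha 0.05 (alpha assumed), power is 0.8993 at N = 205 and 0.9008 at N = 206. The figure reproduces. No sample size or power is stated for the obstetric outcomes.

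**2. How often the rule is triggered by chance.** With k independent tests at 0.05, the chance of at least one p < 0.05 is 1 − 0.95^k.

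| Characteristics | Chance |
|---|---|
| 4 | 18.5% |
| 6 (the named demographic items) | 26.5% |
| 8 (plus EDS and TPDS negative affect) | 33.7% |
| 12 | 46.0% |

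For any single characteristic, such as children in the home, the chance is about 5%.

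**3. Type I error of the unadjusted test.** Let the covariate and outcome test statistics be bivariate normal with correlation ρ (assumed), with no treatment effect; 2,000,000 draws per value of ρ.

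| ρ | Unadjusted, overall | Unadjusted, given p < 0.05 imbalance | Adjusted, given imbalance | Better of the two, given imbalance | Better of the two, overall |
|---|---|---|---|---|---|
| 0.2 | 5.0% | 7.1% | 5.0% | 8.9% | 5.1% |
| 0.3 | 5.0% | 9.6% | 5.0% | 11.8% | 5.1% |
| 0.5 | 5.0% | 18.5% | 5.1% | 21.1% | 5.2% |

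The last two columns suppose that the more favourable analysis is reported when the rule is triggered, for one covariate.

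**4. Size of a chance imbalance.** Assume half the women are first-time mothers. The SD of the arm difference in that share is √(2 × 0.25 / n).

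- n = 103 per arm: √(0.5/103) = 0.070; × 1.96 = 0.137, or 13.7 points.
- n = 400 per arm (the number the protocol expects to be allocated): √(0.5/400) = 0.0354; × 1.96 = 0.069, or 6.9 points.

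Assume that use of anesthesia differs by 15 to 35 points between first-time and other mothers. At the 95% limit, the arm difference then shifts by:

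- 103 per arm: 0.137 × 0.15 = 0.021 to 0.137 × 0.35 = 0.048, so about 2 to 5 points.
- 400 per arm: 0.069 × 0.15 = 0.010 to 0.069 × 0.35 = 0.024, so about 1 to 2.4 points.

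These are extremes, not typical values. The limit is also about where the p < 0.05 rule is triggered.

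**5. Power.** Simulation of 8,000 trials with 103 per arm and a true odds ratio of 0.45 (assumed), comparing Pearson Chi Square with a likelihood-ratio test in logistic regression on arm and first-time status:

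| Assumed rates (other / first-time mothers) | Chi Square | Logistic regression |
|---|---|---|
| 20% / 35% | 0.61 | 0.62 |
| 15% / 40% | 0.58 | 0.61 |
| 10% / 45% | 0.53 | 0.59 |

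Separate runs of 3,000 and 6,000 trials agree to within about one point. In the first row, to three decimals, Pearson gives 0.607, an unadjusted likelihood-ratio test 0.616 and the adjusted model 0.625. About half of that gain therefore comes from the type of test and not from the covariate.

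**The case against.** The case for leaving the text alone is a serious one.

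- **The conflict is conditional.** If no characteristic differs at p < 0.05, the named tests follow the plan exactly. The next paragraph opens with the main analyses and names models that can take covariates, so the rule may have been meant for those. This stands as a possible reading. But the text does not limit the rule, and the tertiary tests come after it.
- **Validity.** A reader might infer that the unadjusted obstetric comparisons are invalid or biased. The documents do not support that: under randomisation with all women analysed, overall type I error is about 5%. The 7% to 19% in the working applies only once a significant imbalance has been observed in a covariate related to the outcome.
- **Size.** The first-time share, the rate gaps and the odds ratio are assumptions. The gain in power is small, and in the mildest scenario about half of it is due to the form of the test. This stands.
- **Denominator.** Obstetric data are collected within the cohort for both arms, all analyses are by intention to treat, and 400 women per arm are expected to be allocated. Then 103 per arm is too few and the shift is halved. If instead only the consenting 35% of the intervention arm were analysed, imbalance would come from selection, and neither the chance-imbalance calculation nor the 5% would apply. The documents do not settle which is meant for these outcomes.
- **Level of detail.** A condensed article may leave covariate sets to an analysis plan. That would answer a complaint about omission. Here both the rule and the tests are printed, and they collide.

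**Conclusion.** The point holds as a conditional conflict within one section. When any baseline characteristic differs at p < 0.05, the tertiary analyses cannot obey both the rule and the named tests. By chance alone this occurs in roughly 27% to 34% of trials with six to eight characteristics, if the tests are independent. Many of those characteristics may have little bearing on birth outcomes.

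The consequence is a model chosen after the imbalance is seen, plus a modest loss of precision: about 1 to 6 points of power at 103 per arm under the assumed rates. It would go too far to say that the two rules can never both be met, or that the obstetric results would be unreliable as planned. Because these outcomes are tertiary, with no stated hypothesis and no power calculation, the priority is low to moderate.

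**What to change.** In Statistical analyses, and in the matching sentence of the abstract, for the tertiary outcomes:

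1. Replace the t-tests by linear regression (gestational age at birth, birth weight) and the Chi Square tests by logistic regression (use of anesthesia, mode of delivery), multinomial if mode of delivery has more than two categories.
2. Include arm and one covariate fixed in advance: number of children in the home at 12 weeks, none versus one or more, as a proxy for earlier births.
3. State that this fixed covariate replaces the p < 0.05 adjustment rule for these outcomes. Without this sentence, an imbalance in age or education would still call for a data-driven change.
4. Report adjusted differences with 95% confidence intervals, and a risk difference beside each odds ratio.
5. Do not adjust birth weight for gestational age at birth, which arises after randomisation.

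The cost is a few sentences; the covariate is already collected in both arms. There are two downsides. The odds ratio becomes conditional on the covariate, which is why a risk difference should accompany it. And children in the home is only a proxy for earlier births.
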